## Research objectives, scope and research questions

2

The COINCIDE study investigates the effect of Indonesia's colistin ban in livestock as an intervention to assess its impact on colistin resistance in *E. coli* from humans and poultry in Indonesia, as well as broader impacts associated with the ban. This project addresses this central question through four integrated perspectives: policy, sociocultural, epidemiological, and molecular approaches. The study scheme, consisting of work packages (WPs) aligned with specific research focus areas and their respective questions and methodologies within the multidisciplinary COINCIDE project, is shown in Fig. 3.

**Fig. 3 f0015:**
[figure not shown]
Overview of the workflow and COINCIDE work package themes, including details on the number of bacterial strains.

*E. coli* is used as an indicator organism in this study because it is commonly found in the intestines of humans and animals, is widespread in the environment, and serves as a key indicator in global AMR surveillance [39]*.* The first work package (WP1) includes coordination, and regulatory affairs. The pre-ban and post-ban sample collection (WP2 and WP3) focus on determining the prevalence of colistin-resistant *E. coli* before and after the ban by collecting and characterizing bacterial isolates from poultry (broiler and layer) and humans. Whole-genome sequencing (WGS) and bioinformatic analysis (WP4 and WP5) will explain resistance mechanisms, molecular epidemiology, and transmission pathways.

The social science work package (WP6) will contextualize epidemiological and molecular findings and investigate colistin and AMU within broader sociocultural contexts. WP6 examines how adherence to public health interventions and their effectiveness are shaped by social and cultural factors, including perceptions of drug efficacy and safety, illness severity, healthcare provider choice, gender and socioeconomic inequalities, historical experiences, and trust in health systems and government. Access-related factors such as drug availability and affordability further drive antimicrobial misuse. These socioecological determinants of AMU and AMR remain underexplored in Indonesia. Social science research is therefore essential to understand community-level drivers of broader AMU and colistin use among farmers, healthcare workers, and community members, as well as the acceptability of interventions, such as the colistin ban, and adherence to them.

Ultimately, this integrated approach aims to provide a comprehensive understanding of the impact of the colistin ban from multiple perspectives and critical evidence to guide future strategies for reducing AMU in livestock and humans in Indonesia.

## Methods

3

### Study design and setting

3.1

The COINCIDE study adopts a cross-sectional comparative design embedded within a One Health framework, supporting simultaneous assessment of colistin resistance and AMU across human and poultry sectors. Sampling will be conducted prospectively and compared with archived pre-ban data collected in 2014. Three districts in Central Java, Sukoharjo, Klaten, and Karanganyar are selected as study locations to maintain consistency with pre-ban data collection from layer farms in Central Java, Indonesia (Fig. 4). These districts provide a diverse social, cultural, and economic setting, where small-scale livestock farming, local health-seeking behaviors, and routine antimicrobials use create an ideal context for studying community- and farm-level antimicrobial practices.

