One promising strategy to reduce AMR in One Health context is the withdrawal and restriction of antimicrobials used in animals through comprehensive policy and regulatory action [12]. Globally, regions such as Europe and North America have successfully reduced AMU and AMR by banning antimicrobial growth promoters (AGPs) and prophylactic use in livestock [13], [14]. In Indonesia, a key milestone was the 2017 NAP-AMR, confirming its commitment to advancing multisectoral One Health collaboration. Building on this NAP-AMR, the Indonesian government banned AGPs in 2018 under the Livestock and Health Law, which states “every person is prohibited from using feed ingredients mixed with certain hormones or antibiotics” [15]. More recently, in response to the detection of colistin use and colistin-resistant *E. coli* in healthy poultry through national AMR surveillance, Indonesian issued a ban on colistin use in livestock in 2020 [16], [17]. A summary of global and national interventions is presented in Fig. 1.

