**Fig. 1 f0005:**
[figure not shown]
Roadmap showing key milestones in the withdrawal and restriction of antimicrobial use in animals through global policies and legislation, aimed at reducing antimicrobial resistance in humans and animals [13], [14], [18], [19], [20], [21], [22], [23], [24], [25].

Colistin, also known as polymyxin E, is a last-resort antimicrobial critical for treating multidrug-resistant Gram-negative infections in humans. Although the clinical use of colistin in humans was limited in the 1980s due to toxicity concerns, the rise of carbapenem-resistant pathogens has renewed its importance [26]. The WHO classified colistin as a highest priority critically important antimicrobial (HP-CIA) for human medicine. However, in many Asian countries, including Indonesia, colistin has been widely used in livestock as a growth promoter and for prophylaxis, further contributing to driving colistin resistance development [27]. The discovery of plasmid-mediated mobilized colistin resistance (*mcr*) genes in 2016 transformed understanding of colistin resistance and AMR transmission, as these genes can spread rapidly between bacteria [28]. In response, countries such as China have restricted colistin use in agriculture, leading to measurable declines in resistance among both animals and humans [24]. Multiple studies from other countries including China, Japan, Portugal, and Spain also showed that banning or restricting colistin use in agriculture leads to a significant reduction in colistin resistance and *mcr*-1 gene prevalence among both animals and humans [29], [30], [31], [32], [33], [34], [35] (Table 1). In the case of Thailand where colistin was banned in 2017, Khine et al. (2022) reported that colistin-resistant *E. coli* prevalence in pigs dropped significantly from 60% in 2017 and 50% in 2018 to 3% in 2019, before rising again to 33% in 2020. In humans, colistin resistant *E. coli* were only detected in 2017 and disappeared in subsequent years [36]. The circulation of colistin resistance after the ban was observed in places like Thailand and it may be due to weak law enforcement and poor compliance with the colistin ban, as regulatory frameworks in Southeast Asia region are likely to be insufficient to ensure effective implementation [37].

**Table 1 t0005:** Prevalence change of *mcr* genes before colistin ban and colistin resistance across countries and sample types (MIC = minimum inhibitory concentration).

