Country	Sample (Bacterial species)	Colistin resistance	Study period	Prevalence change (%)	Reference
China	Human hospital patients (*E. coli*)	*mcr-1*	2016–2019	14.3 → 6.3	[24]
China	Human community (*E. coli*)	MIC	2015–2019	1.7 → 1.3	
China	Pigs (*E. coli*)	MIC	2015–2018	34.0 → 5.1	
China	Chickens (*E. coli*)	MIC	2015–2018	18.1 → 5.0	
China	Pigs (*E. coli*)	*mcr-1*	2015–2019	38–45 → < 2	[29]
China	Broiler chickens (*E. coli*)	*mcr-1*	2016–2019	12.6 → 0.9	[35]
China	Pigs (*E. coli*)	*mcr-1*	2016–2018	45 → 19	[38]
China	Pigs (*E. coli*)	*mcr-1*	2017–2018	86.4 → 5.6	[34]
China	Human healthy volunteers (*E. coli*)	*mcr-1*	2018–2019	11.5 → 2.4	[30]
Japan	Pigs (*E. coli*)	*mcr-1*	2017–2018	17.8 → 6.7	[31]
Portugal	Poultry meat (Enterobacterales)	*mcr-1*	2020–2021	60 → 24	[33]
Spain	Healthy pigs (PCR only)	*mcr-1*	2017–2021	54 → 17	[32]
Thailand	Piglets and human (*E. coli*)	*mcr-1*	2017–2020	Piglets 60 (2017) → 3 (2019) → 33 (2020) Human 40 (2017) → 0 (2020)	[36]

Colistin was banned for use in livestock in Indonesia on July 1st, 2020. This policy ban provides a unique and timely opportunity to assess the effectiveness of such a policy in reducing AMR given its large poultry sector, prior colistin use and distinct regulatory and sociodemographic context (Fig. 2).

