### Sample size and sampling strategies

3.2

To detect a meaningful reduction in colistin resistance from an estimated 15% before the ban to 10% afterward, power calculations indicated the need to analyze at least 683 *E. coli* isolates and risk factor surveys from both human and poultry sources. The retrospective (pre-ban) isolates include 577 archived human isolates from primary health care centers (PHC), 2182 broiler surveillance isolates, 513 layer chicken isolates, and 63 layer farmer isolates from 2014. Regarding the prospective sampling, human participants (*n* = 683) will be recruited from PHC, with eligibility criteria including adults over 18 years without current diarrhea or vomiting, who provide informed consent for rectal swab collection. Random selection via raffles of clinic attendees meeting these criteria will be used to minimize selection bias.

Up to 60 small-scale laying hen farms will be sampled to get an estimated 683 bacterial isolates, identified through local livestock office records. The small-scale layer farm is defined as having fewer than 10,000 layer chickens. Boot swabs will be collected from poultry houses. Farm workers (two or three from each farm, *n* = 120) will also be invited to provide rectal swab samples, enabling paired human-animal analysis. We will document recruitment and refusal rates in each setting to assess potential selection bias. All field teams will follow standard operating procedures developed by the COINCIDE consortium for sample labeling, cold-chain maintenance, and data recording to ensure quality and traceability. Additionally, available AMR data from the national broiler surveillance program from 2018 to 2023 will be incorporated. Within this surveillance program, approximately 800 caecal samples are collected from broilers per year via regional Disease Investigation Centers. From these samples, *E. coli* is isolated, and these isolates are tested for antimicrobial susceptibility including colistin using broth microdilution. These data provides a national perspective on resistance trends before and after the ban.

The complete COINCIDE sample scheme is also illustrated in Fig. 3.

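### With a single 2014 baseline and the 2018 growth-promoter ban in between, a change in humans or layers cannot be apportioned to the July 2020 colistin ban

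*Protocol article*

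**What the plan says.** The aim in section 2 is causal. The ban is treated as an intervention whose impact on resistance in human and poultry *E. coli* is to be assessed. Section 4 speaks of evidence on the effectiveness of restriction policies, and the Abstract hopes to inform policy in other Southeast Asian countries.

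Section 3.1 describes the design: "The COINCIDE study adopts a cross-sectional comparative design embedded within a One Health framework". It then fixes the contrast: "Sampling will be conducted prospectively and compared with archived pre-ban data collected in 2014". Section 3.2 gives the pre-ban material as 577 archived human isolates from primary health care centers, plus "2182 broiler surveillance isolates, 513 layer chicken isolates, and 63 layer farmer isolates from 2014". It describes no human or layer sample between 2014 and the post-ban round, and no population outside the ban.

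The Introduction supplies the dates. "Colistin was banned for use in livestock in Indonesia on July 1st, 2020". Before that, "the Indonesian government banned AGPs in 2018 under the Livestock and Health Law". It also says, of many Asian countries including Indonesia, that "colistin has been widely used in livestock as a growth promoter and for prophylaxis".

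Section 3.2 adds national broiler surveillance from 2018 to 2023, tested by broth microdilution. Of this series it says: "These data provides a national perspective on resistance trends before and after the ban".

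**The concern.** On the article's own account, a second policy covering one of colistin's stated livestock uses came into force between the baseline and the intervention under study. About six years of other change also precede the 2020 ban. Two time points without a comparator cannot separate these influences.

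The central conclusion is at stake. The power statement in section 3.2 labels the whole 15% to 10% difference as before versus after the ban. A reader following the plan would report any human or layer difference since 2014 as the effect of the 2020 policy, in a study meant to advise other countries. The error can go either way: credit for a decline that came earlier, or a verdict of no effect when a background rise offset a real benefit.

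**Working it through.** **1. Order of events (all from the article)**

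| Date | Event | Source |
|---|---|---|
| 2014 | Human and layer baseline | 3.1, 3.2 |
| 2018 | Growth-promoter ban; broiler series starts | Introduction; 3.2 |
| 1 July 2020 | Colistin ban | Introduction |
| Post-ban | New human and layer samples | 3.2 |

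Section 3.7 places the 2014 study within work done from 2013 to 2016. All of that precedes 2018, so the order is unaffected.

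**2. What the contrast estimates**

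Let D be post-ban prevalence minus 2014 prevalence. Then D = S + A + B, where S is secular change, A the effect of the 2018 ban and B the effect of the 2020 ban. There is one observed quantity and three unknowns, so B is not identified. For example, if resistance rose by 5 points from 15% and the 2020 ban then lowered it by 5, D = 15 + 5 − 5 − 15 = 0 and a real effect would be missed.

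**3. The plan's own sample size**

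Inputs: 15% and 10% (section 3.2) and alpha 0.05 (section 3.6). A two-sided test and 80% power are assumed, as neither is stated.

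n per period = (1.960 + 0.842)² × (0.15×0.85 + 0.10×0.90) / 0.05² = 7.849 × 0.2175 / 0.0025 = 682.9, or 683.

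This reproduces the stated figure. The arithmetic is sound; the question is what the difference is attributed to.

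**4. How often the contrast would be significant if the 2020 ban did nothing**

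Power = Φ{(|p1 − p2| − 1.96·√[p̄(1−p̄)(1/n1 + 1/n2)]) / √[p1(1−p1)/n1 + p2(1−p2)/n2]}, with p̄ the pooled proportion.

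Take p1 = 15% in 2014 and let p2 be the prevalence already reached by mid-2020 and unchanged after it. The p2 values are assumptions, since the article gives no trend for 2014–2020. For p2 = 12% with 577 versus 683: p̄ = (86.55 + 81.96)/1260 = 0.1337; the null term is 1.96 × 0.01925 = 0.0377; the denominator is 0.0194; Φ((0.03 − 0.0377)/0.0194) = Φ(−0.40) = 34.5%.

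| Prevalence by mid-2020 | Primary care, 577 vs 683 | Layers, 513 vs 683 (farm clustering ignored) |
|---|---|---|
| 14% | 7.3% | 7.1% |
| 13% | 17.5% | 16.8% |
| 12% | 34.5% | 32.9% |
| 11% | 56.1% | 53.7% |
| 10% | 76.6% | 74.1% |

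The last row is also the power for a true 15% to 10% effect of the 2020 ban. The test responds identically to both situations.

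**5. What the broiler series can offer**

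The Abstract gives 2865 broiler isolates and section 3.2 counts 2182 as pre-ban, so 2865 − 2182 = 683 are post-ban. At about 800 samples a year, January 2018 to June 2020 would give 2.5 × 800 = 2000, roughly in line with 2182. July 2020 to December 2023 would give 3.5 × 800 = 2800, about four times 683. The 683 equal less than one year's intake (683/800 = 0.85).

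If those 683 were spread evenly over 3.5 years (an assumption), there would be about 195 a year or 49 a quarter. At 10% prevalence the 95% half-widths would be 1.96·√(0.09/195) = 4.2 points and 1.96·√(0.09/49) = 8.4 points.

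**The case against.** The strongest objection concerns overreach, and much of it stands. A reader might infer that any fall since 2014 would be wrongly credited to the 2020 ban. The article does not support that. It reports no trend between 2014 and 2020, and it says the 2020 ban followed detection of colistin use and resistance in poultry, so there was use left for it to act on. Part of a fall may well be its effect. A reader might also assume a steady decline and conclude that most of the difference predates July 2020, but such a figure rests on a linear path and a sampling date that the article does not give.

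Nor are the broiler data a clean answer. They start in the year of the growth-promoter ban, so their pre-ban slope may carry its aftermath. A control drug may carry it too, since the law as cited covers antibiotics in feed generally. The stated counts do not support a full post-ban series, only an annual volume is given, and broilers say nothing directly about humans.

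It is also fair that a condensed article leaves model terms to an analysis plan, and that the sentence on broiler trends does not rule out a trend analysis. The use surveys, seller visits and sequencing add context. None of this removes the point. The 2014 comparison and its reading as the ban's effect are fixed in the article itself, and neither an analysis plan nor qualitative work can supply human or layer prevalence between 2014 and 2020.

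**Conclusion.** The point holds in this form: the human and layer contrasts measure change since 2014 and cannot be apportioned between the 2018 measure, the 2020 measure and secular trend. The direction of bias is unknown. Its size cannot be derived from the article. Under the assumed drifts above, a contrast with no contribution from the 2020 ban would be significant between about 7% and 77% of the time. That range illustrates the consequence and does not estimate the bias. The conclusion itself rests only on the stated dates, the single baseline and the absence of a comparator.

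The broiler series is the only described source with data on both sides of July 2020 at less than a six-year remove. It is better evidence on timing, but it does not isolate the 2020 ban.

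**What to change.** 1. In section 3.1 and in the conclusions (Abstract and section 4), describe the human and layer contrasts as change since 2014, reflecting the 2018 and 2020 measures and secular trend together, and not as the effect of the 2020 ban.
2. Make the 2018–2023 broiler data the main quantitative evidence on the timing of change, analysed by isolate sampling date. If dated isolates give enough time points, fit a segmented trend model with a change at 1 July 2020 and a Disease Investigation Center effect. Otherwise report year-by-year prevalence.
3. Run the same analysis in the same isolates for an antimicrobial not targeted by the 2020 ban, as a negative control.
4. State the limits: broilers only; a start in the year of the growth-promoter ban, so the pre-ban trend and the control drug may carry its effect; and about 683 post-ban isolates implied by the stated counts. Explain how that number relates to an intake of about 800 samples a year over the post-ban years.

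This needs no new sampling, but it does need sampling dates for the broiler isolates. The price is a narrower claim for humans and layers, and a wider interval for broilers than a simple before-after contrast would give.

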**Fig. 4 f0020:**
[figure not shown]
COINCIDE study location showing three districts: Klaten, Sukoharjo, and Klaten in the province of Central Java, Indonesia.

### Sample size and sampling strategies

3.2

To detect a meaningful reduction in colistin resistance from an estimated 15% before the ban to 10% afterward, power calculations indicated the need to analyze at least 683 *E. coli* isolates and risk factor surveys from both human and poultry sources. The retrospective (pre-ban) isolates include 577 archived human isolates from primary health care centers (PHC), 2182 broiler surveillance isolates, 513 layer chicken isolates, and 63 layer farmer isolates from 2014. Regarding the prospective sampling, human participants (*n* = 683) will be recruited from PHC, with eligibility criteria including adults over 18 years without current diarrhea or vomiting, who provide informed consent for rectal swab collection. Random selection via raffles of clinic attendees meeting these criteria will be used to minimize selection bias.

Up to 60 small-scale laying hen farms will be sampled to get an estimated 683 bacterial isolates, identified through local livestock office records. The small-scale layer farm is defined as having fewer than 10,000 layer chickens. Boot swabs will be collected from poultry houses. Farm workers (two or three from each farm, *n* = 120) will also be invited to provide rectal swab samples, enabling paired human-animal analysis. We will document recruitment and refusal rates in each setting to assess potential selection bias. All field teams will follow standard operating procedures developed by the COINCIDE consortium for sample labeling, cold-chain maintenance, and data recording to ensure quality and traceability. Additionally, available AMR data from the national broiler surveillance program from 2018 to 2023 will be incorporated. Within this surveillance program, approximately 800 caecal samples are collected from broilers per year via regional Disease Investigation Centers. From these samples, *E. coli* is isolated, and these isolates are tested for antimicrobial susceptibility including colistin using broth microdilution. These data provides a national perspective on resistance trends before and after the ban.

The complete COINCIDE sample scheme is also illustrated in Fig. 3.

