### Data management plan and data analysis

3.6

All data will be securely stored using the Yoda database and ODK data collection forms [40]. Personal identifiers will be pseudonymized or removed to preserve confidentiality. These data will only be available exclusively to principal investigators and data collectors. We will conduct periodic data audits and cleaning to ensure completeness and accuracy. Qualitative data will be analyzed using NVivo version 14. Genomics data will be analyzed using the command line and public bioinformatics resources, where available. All statistical analyses will be carried out using appropriate software such as R version 4.2.3, with a significance level of 0.05, adjusted for multiple testing, applied throughout unless otherwise specified.

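### The required 683 isolates are met only after the ban; the fixed 2014 archives for PHC patients (577) and layers (513) are smaller, so power for 15% to 10% is about 76-77% and 73-74%

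*Protocol article*

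**What the plan says.** Section 3.2 (Sample size and sampling strategies) sets the target: "To detect a meaningful reduction in colistin resistance from an estimated 15% before the ban to 10% afterward", for which "power calculations indicated the need to analyze at least 683" isolates, from human and poultry sources. It does not give the power or the sidedness, and does not say whether 683 is per period, in total or per source.

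The same section lists the pre-ban material: "577 archived human isolates from primary health care centers (PHC), 2182 broiler surveillance isolates", "513 layer chicken isolates, and 63 layer farmer isolates from 2014". Section 3.1 confirms that this side cannot be enlarged: "Sampling will be conducted prospectively and compared with archived pre-ban data collected in 2014".

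For the post-ban side, section 3.2 plans 683 PHC participants, an estimated 683 layer isolates from up to 60 farms, and 120 farm workers. The abstract counts 2865 broiler isolates over 2018-2023; less the 2182 listed as pre-ban, that leaves 683. Section 3.4 takes one colony per human sample and 15 isolates from layer-farm boot swabs. Section 3.6 tests "with a significance level of 0.05, adjusted for multiple testing, applied throughout unless otherwise specified".

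**The concern.** A before-after comparison has two groups, and its precision depends on both. The figure of 683 appears as the post-ban size for PHC patients and layers and, by subtraction, for broilers. Two of the three matching archives hold fewer isolates than that. The archive is also the side with the higher assumed prevalence, and so the larger binomial variance (0.15 x 0.85 = 0.1275 against 0.10 x 0.90 = 0.09), which makes a shortfall there cost more.

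The study exists to judge whether the ban changed resistance. A reader of section 3.2 would take it that each main comparison can detect 15% to 10% with the power behind 683. If that power is lower, a non-significant PHC or layer result says less than the sample size statement implies.

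**Working it through.** **Inputs.** From section 3.2: p1 = 0.15, p2 = 0.10; pre-ban n of 577 (PHC), 513 (layers), 63 (farmers) and 2182 (broilers); post-ban n of 683 (PHC), 683 (layers) and 120 (farm workers). Post-ban broilers: 2865 - 2182 = 683. Alpha 0.05 is from section 3.6. Assumed, because not stated: two-sided test, 80% power, independent isolates, no multiplicity adjustment.

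**Step 1: reproduce 683.** Two independent proportions, unpooled variance, equal groups:

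n = (1.960 + 0.842)² x (0.1275 + 0.09) / 0.05² = 7.849 x 0.2175 / 0.0025 = 682.9, so 683 in each period.

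The pooled-variance formula gives 686. Other common choices move away: continuity-corrected 726, one-sided at 80% power 540, two-sided at 90% power 918 (all with pooled variance). If 683 were the total of both periods (341.5 each), power would be only 51%. The per-period reading is therefore an inference, but a well-supported one.

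**Step 2: power at the actual counts.** Power = Φ(0.05 / √(0.1275/n1 + 0.09/n2) - 1.96), with n1 pre-ban and n2 post-ban. The last column uses the pooled variance under the null.

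| Comparison | n1 v n2 | Standard error | Power, unpooled | Power, pooled |
|---|---|---|---|---|
| Reference | 683 v 683 | 0.01785 | 80.0% | 79.9% |
| PHC | 577 v 683 | 0.01878 | 75.9% | 76.6% |
| Layers | 513 v 683 | 0.01950 | 72.7% | 74.1% |
| Broilers | 2182 v 683 | 0.01379 | 95.2% | 93.0% |
| Farmers | 63 v 120 | 0.05267 | 15.6% | 18.1% |

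For PHC, for example: 0.1275/577 + 0.09/683 = 0.000221 + 0.000132 = 0.000353; its square root is 0.01878; 0.05/0.01878 = 2.662; Φ(2.662 - 1.960) = 75.9%.

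**Step 3: smallest detectable change.** Solving (0.15 - p2) = 2.802 x √(0.1275/n1 + p2(1 - p2)/n2) for p2 gives the post-ban prevalence detectable with 80% power from 15%: about 9.8% for PHC and 9.6% for layers, against 10.0% at 683 v 683.

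**Step 4: can the post-ban side make up for it?** If all 60 farms gave 15 isolates (900), layer power would be 76.4% (unpooled) or 78.9% (pooled), still below 80%. For farmers, even unlimited post-ban sampling gives Φ(0.05/√(0.1275/63) - 1.96), about 20%, because the 63 archived isolates set the limit.

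**Step 5: factors not counted above.** Isolates from one farm are likely to be correlated. The article gives no intracluster correlation. With 683/60, about 11.4 isolates per farm, taken as an assumption for both periods, the design effect is 1 + 10.4 x ICC. Layer power (pooled) is then about 66% at an ICC of 0.02, 56% at 0.05 and 45% at 0.10. The multiplicity adjustment in section 3.6 would lower every figure further.

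**The case against.** The best case for the plan has five parts.

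- **The target may be meant by sector.** Section 3.2 speaks of human and poultry sources. If PHC and farmer isolates formed one human comparison, it would be 63 + 577 = 640 v 120 + 683 = 803, with power of 80.9% (unpooled) or 81.8% (pooled). Broilers are above 80% in any case. A reader might therefore infer that no human comparison can reach the intended power, and the documents do not support that. What stands is that the article describes no such pooling and lists the two groups separately, and that layers fall short on their own counts.
- **Farmers were never sized for this test.** A reader might take the 16-18% as a failed power claim. The article makes no such claim: farm workers are not recruited to 683, and their stated purpose is paired human-animal analysis. The figure is a caution about interpretation and does not drive the severity.
- **The shortfall is small in prevalence terms.** The detectable post-ban level moves from 10.0% to 9.8% or 9.6%. This is fair, and it is why the point is moderate.
- **The assumed 15% is a separate matter.** Table 1 has a human community row with a 1.7% baseline, and a reader might infer that PHC power collapses. Power at so low a baseline would be about as poor with a full 683 in each period, so it is not a consequence of the archive sizes. Other human rows in Table 1 start at 11.5%, 14.3% and 40%, by *mcr-1* rather than by MIC. Nor does the article report colistin results for the 2014 human or layer isolates, so putting an observed baseline in place of 15% could require laboratory testing first.
- **A journal article condenses.** A full power table may well sit elsewhere. That excuses the absence of a table, but not a stated requirement that the counts in the same paragraph do not meet.

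**Conclusion.** The concern holds in a limited form, with moderate severity. Read per period, the requirement of at least 683 is met after the ban and missed before it for PHC patients (577) and layers (513). Power to detect 15% to 10% is about 76-77% and 73-74%, a loss of roughly 3-4 and 6-7 percentage points from 80%. This rests on a two-sided 0.05 test, on 80% power and the per-period reading (both inferred from the reproduction of 683), and on independent isolates at unadjusted alpha. The last two make the figures optimistic, most of all for layers. Broilers are adequately sized on the same assumptions. A farmer before-after comparison could not be informative as a test, but the article does not present it as one.

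**What to change.** In section 3.2, state that 683 is the number per period and give the power and sidedness behind it. Replace the single statement with one line per population (PHC, layers, broilers) at the actual pre-ban and post-ban counts. Each line should give either the power for 15% to 10% or the smallest post-ban prevalence detectable from 15% (about 9.8% for PHC and 9.6% for layers, with independent isolates). Say whether these figures allow for clustering within farms and for the multiplicity adjustment in section 3.6. If PHC and farmer isolates are meant to form one human comparison, say so and give its counts. Describe any farmer before-after comparison (63 v 120) as descriptive, reported as an estimate with a confidence interval.

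The assumed 15% can stay as a labelled planning assumption. The cost is wording, and a stated power slightly less favourable than the one 683 implies; no additional recruitment is needed.

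### The 683 isolates are a per-group size, but the fixed pre-ban archives are smaller (577 PHC, 513 layer), so power per source is modestly below the implied 80%, and the farmer before-after comparison (63 v 120) can only be descriptive

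*Protocol article*

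**What the plan says.** Section 3.2 (Sample size and sampling strategies) plans for a "reduction in colistin resistance from an estimated 15% before the ban to 10% afterward" and reports that "power calculations indicated the need to analyze at least 683" isolates from human and poultry sources. It does not state the power, the sidedness, or whether 683 is per group, per period or in total.

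The same paragraph then lists the pre-ban material: "577 archived human isolates from primary health care centers (PHC"), "2182 broiler surveillance isolates", "513 layer chicken isolates, and 63 layer farmer isolates from 2014". On the post-ban side, "human participants (*n* = 683) will be recruited from PHC", up to 60 layer farms are to yield an estimated 683 isolates, and 120 farm workers are invited. Section 3.2 gives the workers' purpose as paired human-animal analysis.

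Section 3.1 (Study design and setting) says that the prospective samples are compared with the archived 2014 data. Section 3.6 tests "with a significance level of 0.05, adjusted for multiple testing".

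**The concern.** A size calculation for two equal groups holds only if both groups reach that size. Here one side is an archive that cannot grow, and three of its four groups are below 683. The post-ban targets for PHC and layers equal the equal-group figure and show no adjustment for the smaller pre-ban side. The required size stated in section 3.2 is therefore not met source by source.

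For PHC and layers, the stake is an accurate statement of what the study can detect. For farmers it is interpretation. They work directly with poultry, and a non-significant before-after result from 63 and 120 people could be read as the ban having had no effect in them, when the data could not have shown the planned reduction.

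**Working it through.** **Inputs.** From section 3.2: p1 = 0.15, p2 = 0.10; pre-ban n = 577 (PHC), 513 (layer), 63 (farmer); post-ban n = 683, 683 and 120. From section 3.6: alpha 0.05, used here before any multiplicity adjustment. Assumed because not stated: two-sided test, 80% power, independent isolates.

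**1. Reproduce 683.** Unpooled variance, equal groups:

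n = (1.960 + 0.8416)² × (0.15×0.85 + 0.10×0.90) / 0.05² = 7.849 × 0.2175 / 0.0025 = 682.9, so 683 **per group**.

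The pooled-variance formula gives 686. Other settings do not match: one-sided at 80% power gives 538-540, two-sided at 90% gives 914-918, and a continuity correction gives 726.

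**2. Power with the actual group sizes.**

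Unpooled: SE = √(0.1275/n1 + 0.09/n2), power = Φ(0.05/SE − 1.960). The pooled version takes the critical value from SE0 = √(p̄(1−p̄)(1/n1 + 1/n2)), with p̄ the weighted mean rate: power = Φ((0.05 − 1.960×SE0)/SE).

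| Source | n1 v n2 | SE | Power, unpooled | Power, pooled |
|---|---|---|---|---|
| PHC | 577 v 683 | 0.01878 | Φ(0.702) = 75.9% | 76.6% |
| Layer | 513 v 683 | 0.01950 | Φ(0.604) = 72.7% | 74.1% |
| Farmer | 63 v 120 | 0.05267 | Φ(−1.011) = 15.6% | 18.1% |

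Fisher's exact test gives 15% for farmers.

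**3. Could more post-ban isolates restore 80%?** With n1 fixed, the unpooled formula needs n2 = 0.09 / (0.05²/7.849 − 0.1275/n1).

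- PHC: 0.09 / (0.00031852 − 0.00022097) = 922.6, so 923 (pooled: 820).
- Layer: 0.09 / (0.00031852 − 0.00024854) = 1286.1, so 1287 (pooled: 968).
- Farmer: 0.1275/63 = 0.00202 already exceeds 0.00032, so no n2 works. With unlimited post-ban farmers, power reaches Φ(0.05/0.0450 − 1.960) = 19.8% (pooled: 29.6%).

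**4. What the planned sizes can detect with 80% power, starting from 15%.**

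- PHC: a post-ban rate of about 9.8%.
- Layer: about 9.6%.
- Farmer: about 1.9% (unpooled) to 3.1% (pooled). Fisher's exact power is 81% at 3% and 90% at 2%.

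**5. Precision for farmers.** The 95% CI half-width at 15% v 10% is 1.960 × 0.05267 = 0.103, or about 10 points, twice the 5-point planned difference.

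**Not included.** Section 3.4 selects 15 isolates from layer-farm boot swabs, and section 3.6 adjusts alpha. Both would lower these figures. The documents give no intracluster correlation, so the clustering effect is not quantified.

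**The case against.** **The sentence names human and poultry sources, not four subgroups.** Pooling humans gives 577 + 63 = 640 before and 683 + 120 = 803 after, with 80.9% (unpooled) to 81.8% (pooled) power. That arithmetic is right. But the article does not say that humans will be pooled, and it sizes post-ban PHC patients and layers at 683 each, which points to sizing by source. Pooling would also mix clinic attendees and farm workers in different proportions: farmers are 63/640 = 10% before and 120/803 = 15% after. What stands is that the wording is unclear; if pooling is meant, it has to be stated.

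**No farmer test is promised.** This stands. The 63 isolates appear in an inventory, and the workers ("Farm workers (two or three from each farm") are recruited for paired analysis. A reader might infer that the plan claims to detect 15% to 10% in farmers; it does not say so. The only basis for a farmer before-after comparison is the general statement in section 3.1.

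**The PHC and layer gaps are small.** This also stands. They are 3 to 7 points below an 80% that the article never states, and the detectable rates move only from 10% to 9.8% and 9.6%. Several falls in the article's Table 1 are far larger (chickens 18.1% to 5.0%, healthy volunteers 11.5% to 2.4%), although the same table also shows a much smaller one in community humans (1.7% to 1.3%). Using 60 × 15 = 900 layer isolates would raise layer power to 76-79%.

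**Power per source may sit in the full protocol or analysis plan.** That may be so. But 683 and the smaller archive counts stand in the same paragraph of the article, and the conflict can be settled there.

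**Conclusion.** The point holds in a limited form. As a per-group, per-period size, 683 is correct for 15% v 10%, but the pre-ban side does not reach it for PHC or layers. Power is about 76-77% and 73-74%, a modest shortfall before clustering or multiplicity adjustment. More post-ban isolates could in principle close it for both sources.

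For farmers, 63 v 120 has about 16-18% power for the plan's own effect, with a ceiling of 20-30%. A reader might infer that the farmer question cannot be answered at any post-ban number. That is true only for 15% v 10% at 80% power; a fall to about 2-3% would be detectable with the planned numbers. Nor do the documents support saying that the plan breaks a farmer sample-size promise, because it makes none.

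These results rest on two-sided 0.05, 80% power (both inferred from the exact match to 683) and independent isolates.

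**What to change.** In section 3.2:

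- State that 683 is per group and per period, with the power and sidedness used.
- Give achieved power by source: PHC 577 v 683, about 76%; layers 513 v 683, about 73%. Alternatively, give the post-ban rates detectable with 80% power, about 9.8% and 9.6%. Say that these are before clustering and multiplicity adjustment.
- State that the farmer before-after comparison is reported only as a difference with its 95% CI, and that the 120 farm workers serve the paired human-animal analysis.
- If PHC patients and farmers are to be pooled, say so.

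The cost is a slightly less favourable stated power for PHC and layers, and no significance claim for the farmer before-after comparison. No extra recruitment or laboratory work is needed.
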